### Randomization Procedure

Eligible participants will be randomly assigned to Group A, Group B or Group C in a 1:1:1 allocation ratio. Randomized sequences will be generated by a biostatistician who will not be involved in this study using SAS software 9.2 (SAS Institute, Cary, NC, USA). The randomization list will be sealed in sequentially numbered opaque envelopes stored in a double-locked cabinet. Randomization will be performed by a research assistant who is not involved in recruitment. The envelopes will be stored separately after random allocation. Only data collection and analysis will be blinded because the participants and clinicians cannot be blinded to the intervention (16). Figure 1 shows the study flow chart.

### Treatment Protocols/Surgical Intervention

All eligible participants who undergo proximal gastrectomy will be randomly assigned to Group A, Group B or Group C in a 1:1:1 allocation ratio. Group A will receive reconstruction surgery with Kamikawa. Group B will receive reconstruction surgery with DTR. Group C will receive reconstruction surgery with a tube-like stomach. Table 1 shows the surgical methods applied in this study.

**Table 1 T1:** This is the surgical methods applied in this study.

	proximal gastrectomy	Kamikawa	double-tract reconstruction	tube-like stomach
Group A	√	√	—	—
Group B	√	—	√	—
Group C	√	—	—	√

According to the Japanese gastric cancer treatment guidelines (7), routine abdominal exploration will be performed to confirm that no cancer cells have been detached, implanted or metastasized. The patients will undergo laparoscopic D2 lymphadenectomy in radical proximal gastrectomy. Based on the Chinese consensus on digestive tract reconstruction after proximal gastrectomy (17), different methods of digestive tract reconstruction will be performed for each group of patients. The three methods of digestive tract reconstruction are described as follows.

The patients in Group A will receive Kamikawa. Lymph nodes will be routinely dissected. The esophagus will be transected, and the lower part of the esophagus will be dissociated at approximately 5 cm. The stomach will be dragged out through a 5 cm long incision made under the belly button or the xiphid process. The proximal stomach will be severed with a linear stapler 3 cm from the distal tumor. An “H”-shaped seromuscular flap (3.0 cm × 3.5 cm) will be marked on the anterior wall of the remnant stomach near the greater curvature of the stomach. The sarcoplasmic flap will be dissected between the submucosa and musculature, and the gastric mucosa “window” with a similar width as the esophagus will be made at the lower edge of the sarcoplasmic flap for anastomosis. Traction will be performed on the esophagus. Three to four stitches will be used to fix the posterior wall of the esophagus, which is 5 cm away from the esophageal stump and the gastric stump at the upper edge of the sarcoplasmic flap. The whole esophagus will be sutured continuously to the gastric mucosa and submucosa. The whole anterior wall of the esophagus and the whole stomach will be sutured intermittently. Both sides of the sarcoplasmic flap will be sutured intermittently in the shape of a “Y” and fixed with the esophagus to cover the anastomosis. The reconstruction process of Kamikawa is shown in Figures 2A–F.

**Figure 2 F2:**
[figure not shown]
Schematic representation of reconstruction surgery of the digestive tract after proximal gastrectomy (**A**) Kamikawa: A “H"-shaped seromuscular flap (3.0 cm × 3.5 cm) will be marked on the anterior wall of the remnant stomach near the greater curvature of the stomach. (**B**) Kamikawa: The sarcoplasmic flap will be dissected between the submucosa and musculature. (**C**) Kamikawa: The gastric mucosa “window” with similar width to the esophagus will be made at the lower edge of the sarcoplasmic flap for anastomosis. Traction will be performed on the esophagus. Three to four stitches will be used to fix the posterior wall of the esophagus which is 5 cm away from the esophageal stump and the gastric stump at the upper edge of the sarcoplasmic flap. (**D**) Kamikawa: The whole esophagus will be sutured continuously with the gastric mucosa and submucosa. (**E**) Kamikawa: The whole anterior wall of the esophagus and the whole stomach will be sutured intermittently. (**F**) Kamikawa: Both sides of the sarcoplasmic flap will be sutured intermittently in the shape of a “Y” and fixed with the esophagus to cover the anastomosis. (**G**) Double-flap reconstruction (**H**) Tube-like stomach reconstruction.

The patients in Group B will receive double-flap reconstruction. Lymph nodes will be routinely dissected and the esophagus will be transected. The tumor and the proximal stomach will be removed. The jejunum and mesenteric vessels will be cut off 20–25 cm away from the Treitz ligament. The esophagus and distal jejunum will be anastomosed. A linear stapler will be used to close the broken jejunum, and the length of the blind-ending will remain 2–3 cm. The proximal jejunum and distal jejunum will be anastomosed at a distance of 45–50 cm beneath the esophagojejunostomy. Side-to-side anastomosis will be performed on the jejunum and the anterior wall of the remnant stomach 10–15 cm away from the anastomosis of the esophagojejunostomy. The resected end of the stomach will be closed. The reconstruction process of DTR is shown in Figure 2G.

The patients in Group C will receive tube-like stomach reconstruction. Lymph nodes will be routinely resected and the esophagus will be transected. The stomach will be cut off by a linear stapler. A curve will be made parallel to the greater curvature of the stomach (3–4 cm from the greater curvature of the stomach) along the side of the lesser curvature of the stomach from the gastric angle to the junction of the gastric fundus and gastric body. The cardia, tumor and part of the lesser curvature of the stomach will be removed. The length of the tube-like stomach is generally approximately 20 cm. The tissue of the lesser curvature of the stomach will be used to insert the stapler at the gastric corner taking care to not cut it off temporarily. The linear stapler will be inserted from the reserved small incision and pierced out from the anterior wall approximately 3.0 cm from the top of the remnant stomach. End-to-side esophagogastric anastomosis will be performed, and the small incision of the remnant stomach will be closed. The reconstruction process of the tube-like stomach is shown in Figure 2H.

### Clinical Data

The medical staff will acquire the clinical data of the patients, and record that on the online electronic platform (Http://www.medresman.org.cn) and in the CRF table. Only the attending physician will know the identity of the patients. The clinical data will include the patients’ general information, previous medical history, previous surgical history, laboratory examination findings, imaging findings, surgical procedures, the incidence of postoperative reflux esophagitis, the incidence of anastomotic leakage, the incidence of anastomotic stenosis, the incidence of postoperative complications, operative time, and intraoperative blood loss. The above results and information will be recorded in the CRF table. Preoperative and postoperative routine blood tests, biochemical indicators and tumor markers will be included in the laboratory examinations. The CRF table reflects a detailed description of the above data.

### Collection, Preservation and Management of the Biochemical Specimens

In this study, blood samples will be collected from the subjects and subsequently tested by the laboratory. All blood samples will be destroyed after testing and will not be stored.

### Sample Size Estimate and Statistical Analysis

Due to the lack of large sample studies comparing the efficacy of Kamikawa, DTR and tube-like stomach reconstruction methods after proximal gastrectomy, we could only estimate the sample size based on the data related to the incidence of postoperative reflux esophagitis in previous literatures. According to the research results of Kuroda et al. (9), the incidence of reflux esophagitis was 0 in patients who received Kamikawa reconstruction. Aburatani et al. (18) showed that the incidence of reflux esophagitis was 10.5% in patients who received DTR reconstruction. Yasuda et al. (10) demonstrated that the incidence of reflux esophagitis was 13.64% in patients who received a tube-like stomach. We designed a superiority study with a superiority margin of 5% (α = 0.05, β = 0.20, 80% power). Eligible participants will be randomly assigned to Group A, Group B or Group C in a 1:1:1 allocation ratio, and thus 53 patients per group will be required. Therefore, the total sample size is 159 for this study. Considering the loss to follow-up for various reasons, we selected the sample size to be 180.

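### The 53 patients per group do not follow from the stated 5% superiority margin; the figure is reproduced only with a margin of zero, so the stated 80% power does not apply to the margin

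*Protocol article*

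**What the plan says.** The section Sample Size Estimate and Statistical Analysis takes three planning rates from earlier studies: "the incidence of reflux esophagitis was 0 in patients who received Kamikawa reconstruction", "the incidence of reflux esophagitis was 10.5% in patients who received DTR reconstruction", and "the incidence of reflux esophagitis was 13.64% in patients who received a tube-like stomach". It then sets the design: "We designed a superiority study with a superiority margin of 5% (α = 0.05, β = 0.20, 80% power". With equal allocation it concludes "and thus 53 patients per group will be required", a total of 159, which is raised to 180 (60 per group) for loss to follow-up.

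The section does not say which pair of arms the calculation concerns, whether α is one- or two-sided, or whether the 5% is an absolute or a relative difference. The Main Objective section describes a comparison of all three reconstructions. Neither that section nor Study Endpoints mentions a margin.

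**The concern.** The paragraph presents 53 as the consequence of its inputs, and one of those inputs is the margin. A superiority margin is subtracted from the assumed difference before sizing. With assumed differences of 10.5 and 13.64 points, subtracting 5 points removes a large share of the effect and should raise the sample size sharply. A figure as low as 53 therefore suggests that the declared hypothesis and the sizing do not belong together.

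What is at stake is the meaning of the 80%. If the primary comparison is tested against the margin, the trial has materially less power than stated. If it is tested against zero, the hypothesis tested is not the one the sizing paragraph declares.

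**Working it through.** **Inputs**, all from Sample Size Estimate and Statistical Analysis: rates A (Kamikawa) 0, B (DTR) 0.105, C (tube-like stomach) 0.1364; α = 0.05; power 80%; margin m = 0.05. Assumptions: the margin is in absolute points, and both one- and two-sided α are shown.

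**Formula (unpooled normal):** n per group = (z_α + z_β)² × [p₁(1−p₁) + p₂(1−p₂)] / (|p₁−p₂| − m)². The first factor is (1.645 + 0.842)² = 6.183 one-sided and (1.960 + 0.842)² = 7.849 two-sided. The variance sum is 0.105 × 0.895 = 0.093975 for A vs B and 0.1364 × 0.8636 = 0.117795 for A vs C.

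**Step 1. Reproduce 53.** Two routes do so, both with m = 0:
- A vs B, one-sided, unpooled: 6.183 × 0.093975 / 0.105² = 52.7, rounded up to 53.
- A vs C, two-sided, pooled variance under the null (mean rate 0.0682): [1.960 × √(2 × 0.0682 × 0.9318) + 0.842 × √0.117795]² / 0.1364² = 52.4, rounded up to 53.

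**Step 2. Put the margin in.**

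| Contrast | Assumed difference | Difference − 5 points | n, one-sided | n, two-sided |
|---|---|---|---|---|
| A vs B | 10.5 | 5.5 | 192.1 → 193 | 243.8 → 244 |
| A vs C | 13.64 | 8.64 | 97.6 → 98 | 123.9 → 124 |
| B vs C | 3.14 | −1.86 | none | none |

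For B vs C the assumed truth lies inside the margin, so no sample size gives power. Pooled and Fleiss-type variances, smaller α levels and A against the mean of B and C also fail to give 53. The most favourable variant tried (A vs C, one-sided, Farrington-Manning score approximation) still needs 79.

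**Step 3. Power against the margin at 53 per group.** Normal approximation: Φ[(|p₁−p₂| − 0.05)/SE − z_α].
- A vs B: SE = √(0.093975/53) = 0.0421 and 0.055/0.0421 = 1.306. Power is Φ(1.306 − 1.645) = 37% one-sided and Φ(1.306 − 1.960) = 26% two-sided.
- A vs C: SE = √(0.117795/53) = 0.0471 and 0.0864/0.0471 = 1.833. Power is 57% one-sided and 45% two-sided.

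The normal approximation is rough when one rate is 0, so the score test was also enumerated exactly. With no events in the Kamikawa arm, it rejects at 6 or more events among 53 in the other arm (one-sided 0.05), or 7 or more (0.025). The binomial tail probabilities are 49% and 32% for A vs B, and 75% and 60% for A vs C.

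**Step 4. Power at 53 with no margin, two-sided 0.05.**

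| Contrast | Normal approximation | Exact enumeration, Pearson test |
|---|---|---|
| A vs B | Φ(0.105/0.0421 − 1.960) = 70% | 82% |
| A vs C | Φ(0.1364/0.0471 − 1.960) = 82% | 94% |
| B vs C | about 7% | – |

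**The case against.** **The margin may be a wording slip.** It appears only in the sizing sentence, and no success rule in the article uses it. If it is a slip, 53 is a defensible number: without a margin, Kamikawa vs tube-like stomach reaches 80% by either method in Step 4, and Kamikawa vs DTR does so by exact enumeration of the Pearson test. This stands, and it limits the point to a mismatch between margin and sample size. It does not remove the mismatch, because the article states the margin as part of the design.

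**The margin may be relative.** The article gives no scale. A relative 5% would multiply the zero-margin sizes by 1/0.95² = 1.108, which turns 52.7 into 58.4 and 52.4 into 58.1. That is far closer than 124 or 244, but it is still not 53.

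**180 are enrolled, not 159.** The extra patients are there to cover losses. With no loss at all, one case passes nominally: Kamikawa vs tube-like stomach at 60 per group, one-sided score test, 84%. That test rejects at 6 events against 0, and the chance of 6 or more among 60 at a true 5% is 7.9%, above the stated α. Requiring 7 events gives 73%. Kamikawa vs DTR at 60 reaches 61% or 44%.

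**Stronger readings.** A reader might infer that the authors used a one-sided Kamikawa vs DTR calculation. Two routes fit, and the document does not decide between them. A reader might also infer that the trial will probably fail against its margin even if the planning rates are right. That does not hold in general: for Kamikawa vs tube-like stomach the exact score test succeeds in 60–75% of trials at 53 per group.

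**Conclusion.** The point holds as an internal inconsistency. The stated margin, rates, α and power do not lead to 53 per group for any pair of arms, and the 80% is not delivered against the margin at that size. The shortfall is large: by the unpooled formula the requirement is roughly twice the stated figure for Kamikawa vs tube-like stomach (98–124 against 53) and about four times for Kamikawa vs DTR (193–244 against 53). DTR vs tube-like stomach is out of reach under the planning rates.

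This rests on reading the margin as absolute points and on a true Kamikawa rate of exactly 0. Any higher true rate shrinks the differences from the other two arms and lowers these powers. It is not a finding that the trial lacks 80% power for every hypothesis, or that it must recruit more patients. An analysis plan could settle the test and its sidedness, but it could not make 53 follow from a 5-point margin.

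**What to change.** Make the margin and the sample size agree, keeping N = 180. There are two ways:

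1. Remove the margin. Define superiority as a non-zero difference at two-sided α = 0.05, name the contrast or contrasts that carry the primary claim, and restate power for the test that will be used. The Step 4 figures serve for 53 per group; give one method and name it, since the normal and exact values differ by about 12 points.
2. Keep the margin. State its scale, the contrast and the sidedness, and replace the 80% with the power that 53 per group really has (Step 3).

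Either way, say that the figures assume a true Kamikawa rate of exactly 0, and do not assert how 53 was obtained unless the original calculation is on file.

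The cost is one rewritten paragraph and no extra patients. Removing the margin changes the declared hypothesis, so it should be recorded as a change. The stated power becomes less favourable if the margin is kept, and for DTR vs tube-like stomach in either case.

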### Study Endpoints

The primary endpoint will be the incidence of postoperative reflux esophagitis.

The secondary endpoints will be the incidence of anastomotic leakage, the incidence of anastomotic stenosis, the incidence of postoperative complications, operative time, and intraoperative blood loss of three reconstruction surgeries (Kamikawa, DTR and tube-like stomach) after proximal gastrectomy. The test and data collection progress of this experiment is shown in Table 2.

**Table 2 T2:** This is the content of each follow-up which are sorted and merged.

Stage	Preoperation	Intraoperation	Postoperation!					
Follow up period	14-1days		1-14 days	1st month	3rd month	6th month	12th month	24th month
Baseline data collected	√	—	—	—	—	—	—	—
Inclusion and exclusion	√	—	—	—	—	—	—	—
Sign informed consent	√	—	—	—	—	—	—	—
Group determination	√	—	—	—	—	—	—	—
Fill in the basic information	√	—	—	—	—	—	—	—
Physical examination	√	—	—	—	—	—	—	—
Imaging examination	√	—	√	—	√	—	√	√
Laboratory examination	√	—	√	√	√	√	√	√
Operation information	—	√	—	—	—	—	—	—
Postoperative pathology	—	√	—	—	—	—	—	—
Safety observation	√	—	√	√	√	√	√	√
Operational observation	√	—	√	—	—	—	—	—
Record adverse events	√	—	√	√	√	√	√	√
Other works	√	√	√	√	√	√	√	√

### Follow-Up

The first follow-up visit will be arranged on the 14th postoperative day. Follow-up will include physical examination, laboratory examination, and imaging examination to determine the occurrence of postoperative complications. Patients will be followed up at 1, 3, 6, 12 and 24 months. The content of each follow-up will be sorted and merged, as presented in Table 2.

### Patient Protection/Written Informed Consent Forms

We will protect the patients’ personal information. We will never publicly disclose the patients’ information except as required by law. We will implement the informed consent process in strict accordance with relevant Chinese laws and regulations. We will obtain preapproval of the informed consent process for this study from the Internal Review Board/independent Ethics Committee prior to patient enrollment, including any changes made during the study. Informed consent will be obtained in writing from each patient once they are enrolled in the study before undergoing treatment. The original informed consent will be kept by the researchers, and additional copies will be given to the patients for the record.

### Monitoring of the Study

Prior to the start of the study, the project leader will visit each research center to discuss the project with its responsible personnel.

During the study, the project leader will regularly contact the project researchers to provide them with technical support and confirm whether the researchers are carrying out the study according to the plan. The project leader will verify the accuracy of the CRF data records by directly accessing the original records of each patient.

Representatives authorized by the project undertaker and the independent ethics committee may visit all centers for systematic and independent review to verify that all research-related practices are managed and that their data are recorded and accurately reported in accordance with the program GCP and ICH guidelines.

### Patient and Public Involvement

Patients and the public will not be involved in our studies for reporting, designing or implementing.

## Discussion

At present, proximal gastrectomy is increasingly used in the treatment of early proximal gastric cancer, and in some studies, it has shown a better therapeutic effect than total gastrectomy (5, 19–21). However, proximal gastrectomy could cause postoperative complications, especially reflux esophagitis, which has a serious impact on postoperative quality of life among patients (6, 22). Appropriate reconstruction of the digestive tract after proximal gastrectomy can effectively reduce the occurrence of these postoperative complications. Therefore, it is important to select the appropriate method of digestive tract reconstruction after proximal gastrectomy.

Currently, the commonly used methods of digestive tract reconstruction after proximal gastrectomy include EG, JI, JPI and DTR (6). However, there is still no standardized clinical consensus on selecting of reconstruction methods after proximal gastrectomy. Muraoka et al. (23) showed that Kamikawa reconstruction reduced the risk of reflux esophagitis after proximal gastrectomy by increasing the pressure on the lower esophagus of the patients. In their study, none of the patients undergoing Kamikawa reconstruction developed reflux symptoms, which proved that this method of reconstruction was safe and feasible. Aburatani et al. (18) showed that DTR, as one of the reconstruction methods after proximal gastrectomy, had an excellent effect in reducing the incidence of postoperative complications, especially in preventing reflux esophagitis and anastomotic stenosis. Shiraishi et al. (24) showed that a tube-like stomach could prevent reflux esophagitis after proximal gastrectomy by maintaining the basic anatomical structure of the stomach, and could improve the postoperative quality of life of patients compared with traditional esophagogastric anastomosis.

Although the methods above have their own individual advantages, there is still a lack of clinical research on Kamikawa, DTR and tube-like stomach reconstruction after proximal gastrectomy. This study will establish a large-sample, prospective, randomized controlled trial to compare the efficacy of Kamikawa, DTR, and tube-like stomach reconstruction after proximal gastrectomy. Our work may provide more evidence-based medical evidence for the selection of digestive tract reconstruction after proximal gastrectomy.

If the results of this research are in line with our expectations, it will provide a landmark reference for medical staff to improve the prognosis of patients with gastrointestinal reconstruction after proximal gastrectomy. We hope to gain experience from this study and integrate these results into clinical activities and create standardized treatment protocols to guide clinical practice and further improve the postoperative quality of life of these patients.

## Advantages and Limitations of This Study

Advantages: This is the first prospective large sample multicenter RCT to systematically compare the efficacy of three reconstruction methods of the digestive tract (Kamikawa versus DTR versus tube-like stomach) after proximal gastrectomy. Previous studies were mostly retrospective studies (25–27). A few prospective studies focused only on comparing the two reconstruction methods (28, 29).

Limitations: Japanese guidelines recommend that commonly used methods of gastrointestinal reconstruction after proximal gastrectomy include esophagogastrotomy (EG), jejunal interposition (JI), jejunal pouch interposition (JPI) and double-tract reconstruction (DTR) (7). Kamikawa and tube-like stomach were also considered as promising methods. However, we compared only three of these reconstruction methods in our study.

## Data Availability

The original contributions presented in the study are included in the article/Supplementary Material, further inquiries can be directed to the corresponding author/s.
